### **3.2.3 Exploratory Outcome Measures**

- T cell responses against the malaria circumsporozoite antigen by Elispot at days 0, 28, 56, 84, 112 and 140.
- T cell responses against the malaria circumsporozoite antigen by Flow Cytometry at days 0, 28, 56, 84, 112 and 140.
- T cell responses against the malaria circumsporozoite antigen by a whole blood assays to measure secreted cytokines at days 0, 28, 56, 84, 112 and 140.

## 4 STUDY DESIGN

The study is a single-center, double-blinded, dosage-escalation clinical trial to assess the safety of four ascending dosages of Adenovirus Type 35 circumsporozoite malaria vaccine administered in 3 doses intramuscularly. We propose to confirm the safety of each dosage of the new vaccine by assessing safety laboratory parameters and reactogenicity for 14 days after the initial dose in the lower dosages before escalating to the next dosage level. Each dosage level group will include 10 subjects given vaccine intramuscularly. Two subjects in each dosage group will receive normal saline as placebo control.

| Group | Vaccine Formulation                   | Number of Vaccine/Placebo |
|-------|---------------------------------------|---------------------------|
| A     | Ad35.CS.01 – $10^9$ vp/mL             | 10/2                      |
| B     | Ad35.CS.01 – $10^{10}$ vp/mL          | 10/2                      |
| C     | Ad35.CS.01 – $5 \times 10^{10}$ vp/mL | 10/2                      |
| D     | Ad35.CS.01 – $10^{11}$ vp/mL          | 10/2                      |
| Total |                                       | 40/8                      |

## 5 STUDY POPULATION

The study will be carried out by the PDVAP/CNRFP in the Saponé health district in the Bazèga province. This rural area is situated 50 km south west of Ouagadougou, the capital city of Burkina Faso in the Sudan-Sahelian eco-climatic zone. The PDVAP/CNRFP has been conducting epidemiological studies in the area last year. A vaccinology unit specifically dedicated for vaccine trials has been built. The PDVAP/CNRFP has further established demographic surveillance system within Saponé health district (87,678 inhabitants living 79 villages around Balonghin). Through this system, data on vital events and basic malariometric parameters have been collected for a deeper and reliable baseline data necessary for potentials malaria phase 1, 2 or 3 vaccines trials.

In this area malaria transmission is markedly seasonal and intense during the rainy season from June to October. The entomological inoculation rate is above one infective bite/person/night during the intense transmission season and drops to 0 during the low season (dry season). The main malaria vectors are *Anopheles gambiae*, *An. Arabiensis* and *An. funestus*. *P falciparum* accounts for about 90% of malaria infections. The first line treatment for uncomplicated malaria in Burkina is Artemether-Lumefantrine or Artesunate-Amodiaquine. Bed nets are rarely used in the DSS area with less than 5% of the population owning a net.

### 5.1 Selection of the study population

From the up to date database of the population in the study area, a list of all adults 18-45 years old from the village of Balonghin and neighbour villages will be drawn. Subjects will be visited at home by field workers who will explain the study to them. They will then be invited to the vaccinology unit based at Balonghin village to receive more information about the study. An educational process will be instituted which will represent several levels of authority starting from the civil authorities to the local village leadership and down to small groups and ultimately individual. Those who provide a signed informed consent will be screened for study eligibility. A total of 48 eligible adults will be enrolled.

In order to establish a bank of PBMC from individuals with known responsiveness against malaria, for use as positive standards in future human cellular assays in studies with malaria vaccine candidates, the informed consent will include a statement that subjects may be approached for an additional blood sampling outside this vaccine trial.

### 5.2 Enrollment Within Each Dosage Cohort

This study will be performed as a randomized, double-blinded, dosage-escalation study. The first dosage cohort consists of 12 subjects: 10 will receive the Ad35.CS.01 malaria vaccine while 2 will receive placebo control product. The subjects in the first cohort will be enrolled as follows: subject #1 followed by subject #2 with a minimum of a 30 minute waiting period between vaccinating subjects. This schedule will allow for assessment of immediate reactions of subject #1 prior to vaccinating subject #2. Following enrollment of subject #2, a minimum of a 2-day waiting period will be required prior to enrollment of the next four subjects. This schedule will allow for further reactogenicity assessment. The minimum 2-day waiting period will continue between each group of four subjects until the enrollment of 12 subjects into the first cohort has been met.

Following the SMC review of 14-day safety data of the first cohort, the second dosage cohort will contain 12 subjects (10 will receive Ad35.CS.01 and 2 will receive normal saline placebo control product). Six subjects will be enrolled, followed by a minimum of a 2-day waiting period before the next six subjects will be enrolled. The minimum 2 day waiting period will continue between each group of six subjects until the enrollment of 12 subjects into the second cohort has been met. This process will be repeated for the third and fourth cohorts.

Enrollment of additional subjects within any dosage cohort will not occur if a halting rule is met. Enrolled subjects who drop out of the study for any reason will not be replaced.

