## **7.3 Follow-up**

### **7.3.1 Day 1 (+1), 2A, Scheduled home visit**

- Study personnel (field workers) will visit the subject at home to solicit local and systemic reactogenicity and concomitant medication information.
- Any spontaneous AEs that have occurred since the last visit will be assessed.

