### **7.3.2 Day 2 (+1), Visit 3**

- Subjects will be evaluated in the clinic 2 days after immunization. Vital signs (axillary temperature, blood pressure, pulse) will be taken, and information regarding systemic and local reactions will be solicited and recorded. An examination of the vaccination site will be performed.
- Any spontaneous AEs that have occurred since the last visit will be assessed..
- A PE will be performed, to include an assessment of lymph nodes, lungs, heart, liver, and spleen. A complete neurologic examination will also be performed, to include assessment of motor function, sensory function, and deep tendon reflexes.
- Obtain subject's interim medical history.

- Concomitant medications will be reviewed and updated, if applicable.
- Subjects will be reminded about scheduled home visits during which field workers record auxiliary temperatures and local and systemic reactions for the 14-day period after vaccination.
- Subjects will be reminded to come back to the study center if they develop any severe reactions (grade 3) during the study.

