If the SMC determines that it is safe to resume the study, but the subject who has already experienced events contributing to another halting rule experiences a SAE, severe AE or laboratory value that is considered by the investigators, ISM, and DMID Medical Monitor to be part of the original reported event, the study will not be halted for this event. If, however, such an event occurs and is considered by the investigators/ISM/DMID Medical Monitor/SMC to be unrelated to the prior event, the study will halt and formal SMC review will occur.

1. If 2 subjects in any single vaccine group experience severe (Grade 3) vaccination site pain/tenderness within 1 week following vaccination;
2. If 2 subjects in any single vaccine group experience moderate (Grade 2 or 3) fever that is associated with the vaccination within 1 week following vaccination;
3. If 2 subjects experience a spontaneously reported adverse event that is graded to be severe (Grade 3) or life-threatening and is associated with vaccination at any time during the follow-up period;
4. If 2 subjects experience a systemic solicited reactogenicity that is graded severe (Grade 3) (other than vaccine-related fever as defined above) within 14 days of vaccination.
5. If 1 subject experiences an SAE judged by an investigator to be associated with vaccination at any point during follow-up;
6. If 2 subjects develop a laboratory value that is considered severe (Grade 3) and that is judged to be associated with vaccination at any point during follow-up;
7. If 1 subject in any vaccine group tests positive for HIV;
8. Any report of new onset of neurologic symptoms. Any other observation occurs that, in the opinion of the PI or NIH/NIAID/DMID, results in a recommendation to halt enrollment and/or further vaccinations.

During clinic visit, the study personnel will ascertain that the reported severity of an AE by the subject meets the predefined criteria of the study of grading the severity of AEs.

If halting rules are triggered and the Internet is not available, then an immediate report will be made by phone and FAX.

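### The 2-day wait between subgroups can run out before the Day-2 clinic assessment it is meant to allow, and no halting-rule check is required before the next subgroup is dosed

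*Protocol*

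**What the plan says.** **The stagger.** Section 5.2 doses cohort A as two single subjects at least 30 minutes apart and then in groups of four. After subject #2, "a minimum of a 2-day waiting period will be required prior to enrollment of the next four subjects", and the same wait applies between the later groups. For the second cohort the rule is "Six subjects will be enrolled, followed by a minimum of a 2-day waiting period before the next six subjects will be enrolled", and this is repeated for the third and fourth. The stated purpose of the 2-day wait in cohort A is: "This schedule will allow for further reactogenicity assessment".

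**The link to the halting rules.** Section 5.2 also says: "Enrollment of additional subjects within any dosage cohort will not occur if a halting rule is met". Section 9.3 stops enrolment and vaccination when a criterion is met. It gives ongoing monitoring of the criteria to the data coordinating centre and allows the site 2 business days to enter reactogenicity and laboratory data.

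**The first assessments after dosing.** Section 7.2 requires at least 30 minutes of clinic observation, promises a home visit on every day without a clinic visit for 14 days, and tells subjects to return if febrile or if a severe reaction develops. The first scheduled home visit is headed "7.3.1 Day 1 (+1), 2A, Scheduled home visit". The first scheduled clinic visit is headed "7.3.2 Day 2 (+1), Visit 3". It includes examination of the vaccination site, a physical examination and a complete neurologic examination.

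**Confirming an event.** Section 9.3 states: "During clinic visit, the study personnel will ascertain that the reported severity of an AE by the subject meets the predefined criteria". Section 9.1.1 has a licensed clinician assess adverse events. Some rules also need a judgement of cause, such as rule 2: "moderate (Grade 2 or 3) fever that is associated with the vaccination within 1 week following vaccination".

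**The concern.** A stagger protects later subjects only if what happened to the earlier ones is known and acted on before the next are dosed. Here the wait has a stated purpose, but the purpose is not made a condition. The clock can run out before the scheduled examination has taken place, and no one at the site is told to compare the findings with the halting rules before release.

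A site following the text exactly could dose the second six subjects of cohort D, at 10^11 vp/mL, before all of the first six have had their clinic examination. Section 2.1.2 reports that Grade 3 reactions occurred in 2 of the first 6 participants at that dosage in the US trial. Section 2.3.1 says the vaccine has not yet been given to semi-immune people.

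**Working it through.** The plan gives no figure to reproduce. The check is a timeline, a count of who is affected, and a search for any text that closes the gap.

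**1. Timing.** Dosing is Day 0.
- Earliest dosing of the next subgroup (section 5.2): Day 2.
- Visit 3 (section 7.3.2): Day 2 at the earliest, Day 3 at the latest.
- Largest gap: 3 − 2 = 1 day, with the next subgroup dosed first.
- If Visit 3 is on Day 2, both events fall on one day and no text orders them.

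This reads the wait as 2 days elapsed. If it means two clear days between dosing dates, the next dosing is on Day 3 at the earliest. The gap is then 3 − 3 = 0 days, but the order on Day 3 is still not fixed.

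**2. Subjects and releases affected.**
- Cohort A: 2, then 4 + 4 + 2, so 10 subjects follow an earlier subgroup, over 3 releases.
- Cohorts B, C and D: 6, then 6, so 3 × 6 = 18 subjects over 3 releases.
- Total: 10 + 18 = 28 of 48 (28/48 = 58%), over 3 + 3 = 6 releases.

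**3. Is there a condition elsewhere?**
- Section 5.2 bars enrolment if a rule is met. That governs what follows once a rule is known to be met. It does not require anyone to look before release.
- Section 9.3 has the coordinating centre monitor the rules from entered data. Entry may come 2 business days after Visit 3. Depending on the weekday of dosing, the entry deadline falls between Day 4 and Day 7, after the earliest release. This delays remote detection, not the site's own knowledge.
- Sections 5.2, 9.4 and 15.4 require review by the safety monitoring committee of 14-day data, but only between dosage levels.
- Home visits are made by field workers. Their record alerts the site, but severity is for a clinician to assess (section 9.1.1), and rules 2, 3 and 6 also need a judgement of association. Section 9.2 lets a licensed clinician make that judgement for non-serious events.

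None of these makes Visit 3, or a halting-rule check, a precondition for dosing the next subgroup.

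**The case against.** The strongest reply is that the protection that matters is already binding. Enrolment may not continue once a rule is met, and a site can hardly obey that without thinking about the rules. Information also arrives early. Field workers visit daily from Day 1, and a home visit covers Day 2 if Visit 3 slips to Day 3. Subjects with fever or a severe reaction are told to come in, and section 7.6 provides for unscheduled visits. Section 9.3 speaks of confirming severity at a clinic visit, not at Visit 3 in particular. The US Grade 3 symptoms began between 4 and 8 hours after dosing, so similar reactions would probably be known well before Day 2. Each new dosage level also has its own committee review.

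All of this stands, and it limits the consequence. It does not supply the missing step, because each safeguard informs the site or acts once a rule is known to be met.

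Three stronger readings are tempting and are not supported:
- **That release falls inside a peak-reaction window of 24 to 72 hours.** Section 2.3.1 says systemic reactions are usually greatest within the first 24 to 72 hours, which does not describe a window opening at 24 hours. A release tied to Visit 3 would also come on Day 2 or 3, so the point does not favour the change.
- **That the chance of meeting rule 4 measures the gap.** With 4 to 6 vaccine recipients among the first six of cohort D, and no Grade 3 reaction on placebo, the binomial chance of at least two Grade 3 systemic reactions is 5% to 11% at an assumed rate of 10%, and 41% to 65% at an assumed 2/6. These figures say how often a halt would be due, not how often the present text would miss it. The US reactions also included diarrhea, which is not a solicited systemic reaction in section 9.1.1.
- **That a site may go on enrolling after a rule is met.** Sections 5.2 and 9.3 forbid it.

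**Conclusion.** The point holds in a limited form. The wait is fixed only as elapsed time. It can end up to 1 day before the scheduled assessment it is meant to allow, or on the same day in no set order. No text requires that assessment and a halting-rule check before the next subgroup is dosed. This affects six releases and 28 of 48 subjects.

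Severity is low. Surveillance is in place and a known rule breach stops enrolment, so what is missing is an explicit release step. The documents give no basis for estimating how often a due halt would be missed. The conclusion rests on reading the wait as 2 days elapsed (with two clear days, only the same-day ordering problem remains) and on the protocol alone. The Manual of Procedures or the committee charter may contain such a check, but neither is available here.

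**What to change.** In section 5.2, release each next subgroup only when both of these are met:

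1. Every subject in the previous subgroup has completed Visit 3. For a missed visit or a withdrawal, accept a documented Day 2 to 3 contact with clinician review, or documented inability to make contact, so that one absent subject cannot block enrolment.
2. The site investigator has documented that no halting rule is met.

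The cost is about 1 day per release and six short sign-offs. No visits, samples or subjects are added.

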### **2.1.2 Clinical Experience**

A Phase 1 randomized, controlled, dosage-escalation trial to evaluate the immunogenicity, safety and reactogenicity in healthy adults 18 to 45 years of age is ongoing in the U.S. Seventy two subjects are randomized in a 5:1 ratio to receive vaccine or normal saline placebo control by the IM route at 0, 1 and 6 months. Fifteen subjects have received vaccine at  $10^8$  vp/mL, 15 subjects have received vaccine at  $10^9$  vp/mL, and 15 subjects have received vaccine at  $10^{10}$  vp/mL. Enrollment of subjects receiving vaccine at  $10^{11}$  vp/mL is ongoing.

One SAE, not associated with vaccination, has been reported; it was a small bowel obstruction related to appendectomy for appendicitis. It resolved without sequelae.

All mild and moderate AEs associated with injection resolved without sequelae. A causal association with vaccine cannot be determined, and the safety data have not been unblinded at this time. There were a total of 5 moderate AEs in 4 subjects associated with time of injection: a right sided paresthesia lasting 24 hours, itchy tongue which resolved, brachial plexopathy lasting 24 hours, anemia (iron deficiency) and diaphoresis which resolved the same day.

In the current ongoing study in the U.S., after evaluation of the first 6 participants of Group  $10^{11}$  vp/mL, it was noted that significant reactions (grade 3) occurred in 2 of the 6 and were considered associated with injection. Symptoms began in the first 8 hours following vaccination, but none occurred in the first 4 hours following vaccination. These symptoms included fever, chills, myalgia, nausea and GI side effects such as diarrhea, that occasionally lasted for several days, was self-limited, and may or may not have been related to the vaccine.

Two individuals, one from Group  $10^8$  vp/mL and one from Group  $10^{11}$  vp/mL, developed Grade 2 signs and symptoms consistent with a brachial plexus neuropathy that was deemed associated with vaccination. For the subject in Group  $10^8$  vp/mL, symptoms began on the day of vaccination for both the 2nd and 3rd vaccinations but resolved within 24 hours without sequelae. For the subject in Group  $10^{11}$  vp/mL, symptoms began within the first week after 2nd vaccination and were resolved by the Day 7 physical examination. Both of these events resolved without sequelae.

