Additional discomforts of this study are those of having blood drawn from an arm vein, IM injection of the vaccine, and possible reactions to the vaccine. Drawing blood causes transient discomfort and may cause fainting. Infection at the site where blood will be drawn or where the vaccination is given is extremely unlikely, but is a potential risk. Bruising at the site of blood drawing may occur, but can be prevented or lessened by applying pressure for several minutes immediately after the blood draw. Intramuscular injection may cause injection site pain, swelling, and redness. Immediate allergic reactions to vaccine, including anaphylaxis, are in general extremely rare (approximately 1 person in 4,000,000), and might occur as a skin rash such as hives, difficulty breathing, fainting, drop in the blood pressure and death. Such reactions can usually be stopped by emergency medications administered by study personnel. Vaccine recipients may develop systemic reactions such as fever, headaches, body aches, and fatigue. These reactions are usually greatest within the first 24 to 72 hours after vaccination and last 1 to 2 days. Analgesics (e.g., aspirin or Tylenol®) and rest will generally relieve or moderate these symptoms. Other hypersensitivity reactions, including Arthus reactions resulting in large local swelling reactions, are also possible.

In the ongoing Ad35.CS.01 Phase 1 study in the U.S., after evaluation of the first 6 participants of Group D, it was noted that significant reactions (grade 3) occurred in 2 of the 6 and were considered associated with vaccination. Symptoms began in the first 8 hours following vaccination, but none occurred in the first 4 hours following vaccination. These symptoms included fever, chills, myalgia, nausea and GI side effects such as diarrhea, which occasionally lasted for several days, were self-limited, and may or may not have been related to the vaccine. In addition, two individuals, one from Group A and one from Group D, developed signs and symptoms consistent with a Grade 2 brachial plexus neuropathy that was deemed associated with vaccination. For the subject in Group A, symptoms began on the day of vaccination for both the 2nd and 3rd vaccinations but resolved within 24 hours without sequelae. For the subject in Group D, symptoms began within the first week after 2nd vaccination and were resolved by the Day 7 physical examination.

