### **7.2 Enrollment/Baseline Day 0, Visit 2**

- Eligibility criteria will be reviewed with subjects. Vital signs (axillary temperature, blood pressure, pulse) and interim medical history will be obtained.
- A targeted PE will be performed if indicated by the medical history.
- Concomitant medications will be recorded.
- A urine pregnancy test will be performed, and negative results, within 24 hours prior to vaccination, will be confirmed on all females of childbearing potential.
- A 50-mL blood sample for humoral and cell-mediated immune assays will be collected from a vein in the arm prior to vaccination.

- A thick smear slide will be prepared from the 50ml blood sample and will be stored to be read for parasitemia at a later time if necessary. Refer to section 8.2.1
- Enrolled subjects will be assigned to receive Ad35.CS.01 vaccine or normal saline placebo control using the dosage specified by their group (A→D, sequentially).
- Subjects will be observed in the clinic for a minimum of 30 minutes following vaccination. After 30 minutes, the vaccination site will be examined, vital signs will be obtained, and the subject will be questioned about the presence of any localized or generalized reactogenicity symptoms.
- Any spontaneous AEs that occur will be assessed.
- Subjects will be informed that a field worker will be visiting them at home every day (other than scheduled clinic visit day) for 14 days post each vaccination to record all medical information.
- Subjects will be instructed to return to the study center if they feel febrile on any individual day or if they develop any severe reactions following vaccination.

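### At 10^11 vp/mL, section 5.2 lets six subjects be dosed before any 2-day wait, despite the Grade 3 reactions the protocol reports at that dosage; a two-subject lead-in for cohort D is a cheap, modest improvement

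*Protocol*

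**What the plan says.** Protocol section 5.2 sets two enrolment patterns.

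- **Cohort A (10^9 vp/mL).** Subject 2 follows subject 1 by at least 30 minutes. Then: "Following enrollment of subject #2, a minimum of a 2-day waiting period will be required prior to enrollment of the next four subjects". Groups of four follow, with 2-day waits, up to 12 subjects.
- **Cohorts B to D.** For the second cohort: "Six subjects will be enrolled, followed by a minimum of a 2-day waiting period before the next six subjects will be enrolled". Then: "This process will be repeated for the third and fourth cohorts". The fourth cohort is 10^11 vp/mL. No interval is set inside a group of six.

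Sections 2.1.2 and 2.3.1 describe the first six US participants at 10^11 vp/mL: "it was noted that significant reactions (grade 3) occurred in 2 of the 6 and were considered associated with injection". On timing: "Symptoms began in the first 8 hours following vaccination, but none occurred in the first 4 hours following vaccination". Section 2.1.2 also records that 15 US subjects had already received 10^9 vp/mL.

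Section 7.2 sets the post-dose observation: "Subjects will be observed in the clinic for a minimum of 30 minutes following vaccination". Under section 7.3.1, on Day 1 (+1), field workers "will visit the subject at home to solicit local and systemic reactogenicity and concomitant medication information". Section 9.3, rule 4, calls for a halt when two subjects have a Grade 3 solicited systemic reaction other than fever within 14 days. Unlike rules 1 and 2, it is not confined to one vaccine group.

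**The concern.** At the only dosage for which the protocol reports a Grade 3 signal, the first obligatory 2-day pause comes after six subjects, not two. Reactions that begin 4 to 8 hours after injection fall outside a 30-minute observation but well inside a 2-day wait. If six are dosed on one day, which section 5.2 permits, nothing learned from the first two can protect the other four. The safety committee review before escalation does not help here, because it covers the dosage below.

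At stake is how many subjects in cohort D receive 10^11 vp/mL before the study can react. No estimate or test is affected.

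**Working it through.** The protocol gives no figure to reproduce here. The size of the effect can be modelled.

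**Inputs**
- Cohort of 12, with 10 vaccine and 2 placebo (sections 4 and 5.2), taken in random order.
- Group sizes: 6+6 as written; 2+4+4+2 as in cohort A (section 5.2; the final 2 follows from the cap of 12).
- Halt at k = 2 cases (section 9.3, rule 4). k = 1 applies if an earlier cohort already had a rule 4 case, or after a review that lets the study proceed. Section 9.3 states this one-further-subject principle with rule 3 as its example.
- Case probability p per vaccinee: assumed 1/3, from 2 of 6. The Clopper-Pearson 95% interval for 2/6 is 0.043 to 0.777.
- Assumed: cases occur in vaccinees only; looks happen only at the 2-day waits; every case is known by the next look.

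**Formula**

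Expected number dosed = sum over groups of (group size) x P(fewer than k cases among the m subjects before that group), where

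P(X_m < k) = sum over v of [C(10,v) C(2,m-v) / C(12,m)] x P(Bin(v,p) < k).

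**Two cases needed, p = 1/3**
- m = 2: both are vaccinees with probability 0.682, so P(<2) = 1 - 0.682 x 1/9 = 0.924.
- m = 6: v = 4, 5, 6 with probability 0.227, 0.545, 0.227, so P(<2) = 0.227 x 0.593 + 0.545 x 0.461 + 0.227 x 0.351 = 0.466.
- m = 10: P(<2) = 0.178.
- 6+6: 6 + 6 x 0.466 = 8.80.
- 2+4+6: 2 + 4 x 0.924 + 6 x 0.466 = 8.49.
- 2+4+4+2: 2 + 4 x 0.924 + 4 x 0.466 + 2 x 0.178 = 7.92.
- Saving 0.88 subjects: 0.30 from the lead-in and 0.58 from splitting the second six.

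**One case enough, p = 1/3**
- P(no case) for m = 2, 6, 10: 0.520, 0.137, 0.035.
- 6+6: 6 + 6 x 0.137 = 6.82.
- 2+4+6: 2 + 4 x 0.520 + 6 x 0.137 = 4.90.
- 2+4+4+2: 2 + 4 x 0.520 + 4 x 0.137 + 2 x 0.035 = 4.70.
- Saving 2.12 subjects, of which the lead-in gives 1.92.

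**Other rates, 6+6 v 2+4+4+2**

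| p | two cases needed | one case enough |
|---|---|---|
| 0.043 | 11.9 v 11.8 | |
| 0.20 | 10.4 v 9.8 | 8.0 v 6.4 |
| 0.40 | 8.1 v 7.1 | 6.5 v 4.1 |
| 0.777 | 6.1 v 4.4 | |

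**The lead-in pair alone, p = 1/3.** At least one case: 1 - 0.520 = 48%. Two cases: 1 - 0.924 = 7.6%. Pair includes a placebo recipient: 1 - 0.682 = 32%.

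**If each six is spaced as 3+3 with an effective look between, p = 1/3.** P(<2) for m = 3 and 9 is 0.813 and 0.230. The expected number is 3 + 3 x 0.813 + 3 x 0.466 + 3 x 0.230 = 7.53, below 7.92. With one case enough, it is 3 + 3 x 0.374 + 3 x 0.137 + 3 x 0.049 = 4.68, about the same as 4.70.

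**The case against.** Section 5.2 is clear and contradicts nothing. Section 2.3.1 says the vaccine has not yet been given to semi-immune subjects, so the tightest stagger in cohort A has a reason even though 10^9 was already given in the US. That stands. A reader might infer that the lead-in was put at the wrong dosage. The documents do not support that; the point is only that cohort D could have the same.

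The US signal is weak evidence. It is 2 of 6, blinded, from malaria-naive adults, self-limited, and by the protocol's own account possibly unrelated to the vaccine. The US injection volume is not given (0.75 mL here), nor is it said which symptoms were Grade 3, while rule 4 excludes fever. All of this stands, and it makes 33% an assumption.

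Cohort D already has protection: a 5 x 10^10 step before it, committee review of 14-day data, Day 1 home visits, the instruction to return with severe reactions, rule 2 on fever, and rule 8, which allows a halt on any observation. The model includes neither rule 2 nor rule 8. A halt also leads to review, after which dosing may resume, so a subject not dosed before the halt may be dosed later. This stands and limits the claim.

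Two larger readings are tempting.
- At 33% the chance of two or more cases before the first wait is 53% with six subjects and 7.6% with two. That drop is not a benefit in itself; it arises because fewer have been dosed by then.
- The one-case saving could be averaged over a guessed chance of an earlier rule 4 case in cohorts A to C. The documents give no rate for that, so no such average should be quoted.

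What the objection does not supply is a reason against a lead-in at 10^11, or any text that requires spacing within a six.

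**Conclusion.** The point holds as a cheap safety improvement worth considering, not as an error that must be corrected. As written, six subjects can receive 10^11 vp/mL before the first 2-day wait; with a lead-in it would be two.

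Under the ordinary two-case rule the gain is small: 0.88 of 12 subjects at an assumed 33%, with only 0.30 due to the lead-in. It is larger, 2.12 subjects, when a single case is enough, but that needs an earlier rule 4 case or a previous review that let the study proceed. Over the interval for 2/6 the two-case saving runs from almost nothing to 1.7 subjects (6.1 - 4.4).

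These figures assume looks only at the 2-day waits. They may represent deferral of dosing only, and at 33% they vanish if the site already spaces each six as 3+3 with an effective look.

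**What to change.** In section 5.2, leave cohorts A to C as they are and give cohort D its own sentence, for example: the fourth cohort starts with one subject and, at least 30 minutes later, a second; groups of four, four and two then follow, each after a pause of at least 2 days.

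The cost is one paragraph of text and about 4 more days of enrolment in cohort D (three 2-day waits instead of one: 6 - 2 = 4). Sample size, visits and randomization do not change, and the site will already have run this scheme in cohort A.
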